### Methods in analysis to handle protocol non-adherence and any statistical methods to handle missing data {20c}

Analysis will follow intention-to-treat principles and missing data may be multiply imputed if the missing data mechanism is considered to be Missing at Random (MAR). We will also conduct a complier average causal effect analysis of the primary outcome.

### Plans to give access to the full protocol, participant level data and statistical code {31c}

An anonymised dataset will be deposited within the University of Sussex Research Repository to facilitate open access for other researchers. The reuse and sharing of anonymised data will be made explicit to participants on the study consent form. Identifiable information will not be shared with anyone outside of the research team.

## Oversight and monitoring

### Composition of the trial steering committee {5d}

A Trial Steering Committee (TSC) will be established according to MRC guidelines [48] and will be chaired by a senior clinical academic. Membership will include at least two independent experts and two independent lay members. The TSC will meet at least annually and will provide overall supervision of the trial, monitoring adherence to the protocol and providing independent advice on all aspects of the trial.

A separate Lived Experience Advisory Panel (LEAP) will provide Patient and Public Involvement (PPI) oversight of the trial. LEAP members will receive training to facilitate their involvement and meet regularly during the course of the study to consult on issues concerning informed consent and participant well-being, development of accessible study materials, recruitment and retention, and the interpretation of findings and dissemination. An ‘involvement log’ will track the influence of the advice offered to the Research Team by the LEAP.

### Composition of the data monitoring committee, its role and reporting structure {21a}

A Data Monitoring & Ethics Committee (DMEC) will meet at least annually and report to the TSC. It will have access to all unblinded trial data and will receive regular reports on adverse events. Membership of the DMEC will be independent of the applicants and of the TSC. An independent senior statistician will be appointed as chair and the group will also comprise independent senior clinical academics. The CI, trial coordinator and the trial statistician will attend parts of the DMEC meeting to provide reports but will not be members of the DMEC.

### Adverse event reporting and harms {22}

Any unfavourable and unintended sign, symptom or illness that develops or worsens during the period of the study will be classified as an adverse event (AE), whether or not it is considered to be related to the study treatment. Adverse events will include: an exacerbation of a pre-existing illness; an increase in the frequency or intensity of a pre-existing episodic event or condition requiring additional contact from care teams; a condition that is detected after trial intervention administration; and continuous persistent disease or a symptom present at baseline that worsens following administration of the trial treatment—and may be expected or unexpected. Serious Adverse Events (SAEs) are those considered to be life-threatening, resulting in death, requiring inpatient hospitalisation or prolongation of existing hospitalisation, resulting in significant or persistent incapacity/disability or a birth defect or congenital abnormality. The number (events and individuals) and nature of all events (AE and SAE) reported to blind and unblind members of the research team will be recorded.

The period for adverse event reporting will be following the signing of the study consent form until last follow-up assessment 28 weeks after randomisation. All AEs will be recorded and reviewed by a Site Lead. If an AE is considered to be serious (an SAE), it will be reviewed for causality and expectedness by the Chief Investigator and an independent rater. The TSC will be informed of the number, nature and review outcome for all SAEs and will be asked to recommend any necessary actions. SAEs will be reported to the Sponsor, DMEC and NHS Research Ethics Committee as appropriate.

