### Intervention description {11a}

#### Guided self-help intervention for voices (GiVE)

The intervention is described in our published workbook [18] and will consist of 10 one-hour sessions of the GiVE intervention over a 16-week period, delivered by APs in NHS clinics, participants’ own homes or other community locations as preferred and appropriate. Where participants express a preference for the intervention to be delivered remotely (by videocall or phone), this preference will be honoured. GiVE is a psychological intervention that targets the mechanisms that have been empirically found to maintain voice-related distress—negative beliefs about voices, [22, 23] negative beliefs about self [24, 25] and negative relating [26, 27]. After the introductory sessions (including a focus upon coping), the intervention will cover three core modules: (1) beliefs about the self, (2) beliefs about voices and (3) relationships. Modules (1) and (2) draw upon psychoeducation and cognitive behavioural strategies to help participants to re-evaluate the accuracy of their negative or unhelpful beliefs related to the self and voices. Module (3) additionally involves work on how to relate to others and voices more assertively.

A participant will have received sufficient ‘exposure’ to the intervention if they have attended a minimum of 6 of the 10 sessions.

Participants will be provided with a copy of the workbook [18] and companion self-help book [17] and will be ‘guided’ through the structured content of the workbook by an AP—with encouragement to complete between-session exercises in the workbook and to read relevant chapters of the self-help book. Participants will also have the opportunity to access the ‘CHOICES’ mobile phone application. The ‘CHOICES’ app was developed by Sussex Partnership NHS Foundation Trust to support the learning of patients within its clinical services. The app has been revised for use in this trial and aims to support the continued use of strategies that have been learnt through the GiVE intervention. If participants have a smart/ iPhone and are familiar with accessing mobile phone apps, the AP will provide them with a guide to access the CHOICES app. The research team will have no access to the data entered by participants into the app.

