### Criteria for discontinuing or modifying allocated interventions {11b}

The intervention may be discontinued if the participant requests this or if the AP judges, in consultation with the wider supervisory team, that the intervention is associated with a significant worsening of mental health. In this case, an adverse event form would also be completed. It will be made clear to each participant that, should they find any aspect of the research distressing, including the intervention, and/or no longer wish to continue, they will be able to withdraw without this impacting on their usual clinical care in any way.

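### By-arm counts of non-serious adverse events are at risk of bias because some reporting routes exist only in the GiVE arm

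*Protocol article*

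**What the plan says.** All points are from the protocol article.

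- **Definition and window** (Adverse event reporting and harms {22}). The general rule is broad. It takes in anything untoward "that develops or worsens during the period of the study will be classified as an adverse event (AE"), related to treatment or not. The window runs from consent to the 28-week follow-up in both arms.
- **Listed inclusions** (same section). Two of the four refer to the intervention. One is "a condition that is detected after trial intervention administration". The other, on worsening from baseline, is "continuous persistent disease or a symptom present at baseline that worsens following administration of the trial treatment".
- **Route into the record** (same section). The number and nature of all events "reported to blind and unblind members of the research team will be recorded". A Site Lead reviews every AE.
- **Contacts in GiVE only** (Guided self-help intervention for voices). The intervention is "10 one-hour sessions of the GiVE intervention over a 16-week period", and sufficient exposure is "a minimum of 6 of the 10 sessions". The section goes on to say that Site Leads supervise the APs weekly.
- **Form in GiVE only** (Criteria for discontinuing or modifying allocated interventions {11b}). The intervention may be stopped at the participant's request, or because the AP judges it to be associated with significant worsening. "In this case, an adverse event form would also be completed".
- **Contacts in both arms** (Plans to promote participant retention {18b}). Assessments after randomisation are at 16 and 28 weeks.

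**The concern.** Recording depends on an event reaching a member of the research team, and the two arms have different amounts of contact with that team. A GiVE participant whose mood dips in week 6 may mention it to an AP, who takes it to a Site Lead, who also reviews AEs. A TAU participant with the same dip has no scheduled research contact until week 16, and may by then have recovered or forgotten it. The form tied to stopping the intervention adds a second route that TAU participants cannot trigger.

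At stake is the harms table. An excess of non-serious AEs in GiVE could come from more contact alone, and a real excess could be dismissed as an effect of contact. This matters for a trial of delivery by briefly trained staff. The Data Monitoring & Ethics Committee also receives regular AE reports with access to unblinded data, so counts by arm may well be compared whether or not a test is planned. The primary efficacy result is not affected.

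**Working it through.** The article gives no figure for harms, so there is none to reproduce. The steps below set out the routes and then illustrate the possible size.

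**1. Routes after randomisation**

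| Route | GiVE | TAU |
|---|---|---|
| Blind research assistant (RA) at 16 and 28 weeks | 2 | 2 |
| AP sessions, full attendance | 10 | 0 |
| AP sessions, at the sufficient-exposure minimum | 6 | 0 |
| AE form on stopping the intervention | possible | not possible |

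Scheduled contacts are 10 + 2 = 12 (or 6 + 2 = 8) in GiVE and 2 in TAU. The telephone call giving the allocation is made in both arms and is left out.

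**2. Model (assumptions, not document values)**

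Let p be the true risk of at least one non-serious AE, equal in both arms. Let q be the chance that any one contact brings it to light, independent across contacts, with no other route. Then

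recorded risk = p × [1 − (1 − q)^k], where k is the number of contacts,

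and p cancels from the ratio:

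recorded risk ratio = [1 − (1 − q)^k_GiVE] / [1 − (1 − q)^2].

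| q | TAU, k = 2 | GiVE, k = 12 | Ratio | GiVE, k = 8 | Ratio |
|---|---|---|---|---|---|
| 0.1 | 0.190 | 0.718 | 3.8 | 0.570 | 3.0 |
| 0.2 | 0.360 | 0.931 | 2.6 | 0.832 | 2.3 |
| 0.3 | 0.510 | 0.986 | 1.9 | 0.942 | 1.85 |
| 0.5 | 0.750 | 1.000 | 1.3 | 0.996 | 1.3 |

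For q = 0.1 and k = 12: 1 − 0.9^12 = 0.718, 1 − 0.9^2 = 0.190, and 0.718/0.190 = 3.8.

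**3. What such a ratio could do at this trial's size**

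Take 65 per arm, p of 0.2 or 0.4 and a two-sided Fisher exact test. With no true difference, the chance of p < 0.05 is 8% to 86% over the same q values at full attendance, and 8% to 66% with 6 sessions. The lowest figure is at q = 0.5 and p = 0.2. At full attendance the highest is at q = 0.1 and p = 0.4, where recorded risks are 0.287 and 0.076. The article plans no such test, so this only shows how far the counts could mislead.

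**4. After the fix**

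Counting only what the two shared assessments bring to light gives k = 2 in both arms, and the ratio under equal true risk is 1.0 for every q.

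**The case against.** Several points on the other side stand.

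- **The definition.** The general rule and the window are arm-neutral, and the listed items illustrate the rule. A TAU participant who worsens is covered by the rule and by the inclusion for exacerbation of existing illness. A reader might infer that AEs are defined through GiVE-only events. The text does not support that: the two items exclude no TAU event, and their fault is wording.
- **No stated comparison.** The article describes no formal between-arm test of harms, and tabulation may be left to the analysis plan. It would therefore be too strong to say that a planned comparison is biased.
- **Sources.** Naming blind and unblinded recipients does not mean that their reports will be pooled. It is equally consistent with keeping the source of each event.
- **The discontinuation form.** Documenting harm when therapy stops is proper practice and creates no new class of AE. It is still a prompt to record that only one arm has.
- **Elicitation.** The full protocol may specify a standard enquiry, so its absence from an article is no finding. This point rests on routes that the article does state.
- **Inherent asymmetry.** Any trial of therapy against usual care has more contact in one arm. That explains the problem but does not make the counts comparable, and separating them by source is a cheap remedy.

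A reader might also infer a six-fold distortion from 12/2 = 6. That is a ratio of contacts, not of events. The recorded ratio approaches 6 only as detection per contact approaches zero with full attendance, and it falls towards 1 as detection improves.

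**Conclusion.** The concern holds as a risk of bias in by-arm counts of non-serious AEs, most likely towards over-recording in GiVE. It follows from routes that the article states: AP sessions, the discontinuation form, and AE review by the Site Leads who supervise the APs.

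Its size cannot be derived from the document. The illustrative range of about 3.8 to 1.3 (3.0 to 1.3 with 6 sessions) rests on equal true risk, an assumed detection of 0.1 to 0.5 that is the same and independent at every contact, and no other route. A thorough retrospective enquiry at the shared assessments, or reports from care teams in both arms, would bring the ratio closer to 1. Deaths and hospitalisations depend less on contact with the team, and serious adverse events (SAEs) are also reviewed by an independent rater.

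The change is worth making because it costs little, and without it the harms table would be hard to interpret.

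**What to change.** 1. Keep the general AE definition and the window from consent to 28 weeks. Reword the two intervention-based inclusions so that they apply to both arms within that window. Re-anchoring them to randomisation would conflict with the consent-based start.
2. Record the source of each event: blind RA, AP, care team or other.
3. Base any between-arm comparison on sources available identically in both arms, namely the blind RA contacts at 16 and 28 weeks, plus SAEs from any source common to both arms.
4. Tabulate events known only through AP contact separately, as GiVE-arm safety data.

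Reporting to the sponsor and the committees is unchanged, and no event is lost from the safety record. The cost is a change of wording and one field on the AE form, plus a common enquiry at the two assessments if none exists already. The article gives recruitment as starting in October 2022 and data collection as running to April 2024. For data already collected, counts can be separated only where the source was kept. The downside is that fewer events enter the comparison, so it will be less precise.

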## Introduction

### Background and rationale {6a}

Approximately 300,000 people in England and Wales have a diagnosis of psychosis [1]. The symptoms of psychosis such as paranoid delusions and hearing voices (hereafter referred to as distressing voices) cause significant distress and disability and contribute to an increased risk of physical health problems and early mortality [2], and suicide rates up to twelve times greater than the general population [3]. The overall annual societal cost of psychosis in England has been estimated at £11.8 billion [4].

Cognitive behaviour therapy for psychosis (CBTp) has robust evidence for clinical [5] and cost-effectiveness [6] and is recommended by the National Institute for Health and Care Excellence (NICE) to promote the recovery of psychosis patients [6]. However, implementation in the UK is extremely poor, [7] with only 26% of psychosis patients being offered CBTp [1]. One reason for this lack of access is limited resources, [8] as CBTp is resource-intensive in relation to its duration (minimum of 16 sessions recommended by NICE) and delivery (by highly trained therapists—who are trained over a 2–3-year period).

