Consistent with the previous recommendations from Experts-by-Experience (EBEs), we will recruit APs who have some experience of working as an AP with patients with complex needs. The APs will receive a brief 3-day training in the delivery of the GiVE intervention facilitated by the Chief Investigator. The training will include 1 introductory day (covering the experience of distressing voices and CBT principles) and 2 days on the GiVE intervention (covering the content of the workbook) and will be delivered to all APs at the same time.

Two APs will offer the GiVE intervention at each site. The APs will be offered weekly clinical supervision by the Site Leads, including both 1:1 supervision at site and group supervision at both site and remotely across sites. Participants in the GiVE arm will continue to receive treatment as usual (described below) throughout their participation in the study.

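### The closed SAE list has no medically-important-event criterion, so a suicide attempt or serious self-harm that meets none of its items misses independent causality review and the SAE report to the TSC

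*Protocol article*

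**What the plan says.** All of the wording at issue is in the protocol article, mainly under Adverse event reporting and harms {22}.

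- **What an AE is:** "Any unfavourable and unintended sign, symptom or illness that develops or worsens during the period of the study", whether or not it is thought to be related to treatment. Examples follow, such as worsening of an existing illness.
- **What an SAE is:** "Serious Adverse Events (SAEs) are those considered to be life-threatening, resulting in death, requiring inpatient hospitalisation or prolongation of existing hospitalisation", and then "resulting in significant or persistent incapacity/disability or a birth defect or congenital abnormality". The list ends there.
- **Review of every AE:** "All AEs will be recorded and reviewed by a Site Lead".
- **Added review for an SAE:** "it will be reviewed for causality and expectedness by the Chief Investigator and an independent rater".
- **TSC:** "The TSC will be informed of the number, nature and review outcome for all SAEs". The TSC may then recommend action. SAEs also go to the Sponsor, the DMEC and the ethics committee as appropriate.

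Three other sections bear on this. The intervention description {11a} says of the therapists, who are assistant psychologists (APs): "The APs will be offered weekly clinical supervision by the Site Leads". The section on the data monitoring committee {21a} gives the DMEC the unblinded data and regular AE reports, and makes it independent of the applicants and the TSC. The Background {6a} describes a population with "suicide rates up to twelve times greater than the general population".

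**The concern.** The classification of an event decides who looks at it. An SAE is assessed for cause and expectedness by two people, one of them described as independent, and is reported to the TSC. For any other AE, the only individual review stated is by a Site Lead.

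Every item on the SAE list is a specific medical consequence. No item lets a reviewer call an event serious because of what it is. A suicide attempt followed by same-day discharge or community support can meet none of the items. In a population whose raised suicide rate the protocol itself cites, that is a foreseeable kind of event and one that a reader of the safety results would want assessed independently.

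At stake is the completeness of the SAE table, and whether a possible link to the intervention is judged by someone outside its delivery.

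**Working it through.** The documents give no figure to reproduce, and no arithmetic applies to the classification. The check applies the stated wording to types of event.

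**1. Is the list closed?** The AE paragraph gives examples and says that AEs will include them, which leaves that list open. The SAE sentence says what SAEs are, names five consequences (threat to life, death, admission or its prolongation, incapacity or disability, birth defect or abnormality) and adds no residual category. Read as written, it is exhaustive.

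**2. How are events classed and routed?**

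| Event after consent | SAE item met | Class | Chief Investigator and independent rater | SAE report to TSC | DMEC |
|---|---|---|---|---|---|
| Attempt judged life-threatening, no admission | Threat to life | SAE | Yes | Yes | Yes |
| Attempt or self-harm leading to admission | Admission | SAE | Yes | Yes | Yes |
| Attempt or self-harm with lasting incapacity | Incapacity | SAE | Yes | Yes | Yes |
| Attempt or serious self-harm, not judged life-threatening, no admission, no lasting incapacity | None | Non-serious AE | No | No | Through AE reports and data access |
| Serious harm to another person, participant not admitted | None | Not clearly an AE | No | No | Uncertain |

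The fourth row is the gap. The fifth is a different problem: the AE definition speaks of a sign, symptom or illness, so an act against someone else may fall outside it altogether.

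**3. What review is left in the fourth row?** Site Leads review all AEs under {22}. Under {11a} they also supervise the therapists every week, so the reviewer is not separate from delivery. The Chief Investigator, who reviews SAEs, trains the therapists, also under {11a}. The independent rater is therefore the only case-level reviewer whom the text describes as independent, and a fourth-row event does not reach that person.

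**4. What does the DMEC add?** Under {21a} it is independent, can see the unblinded data, receives regular AE reports and reports to the TSC. A fourth-row event can therefore come before it. However, the DMEC need meet only once a year, and no causality rating is specified for non-serious AEs. The case may reach it without the assessment that an SAE would carry.

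**5. Can the number be estimated?** The count would be 130 × p × q, where 130 is the recruitment target in Sample size {14}, p is the proportion with a suicide attempt or serious self-harm during the reporting period, and q is the share of those meeting no SAE item. The documents give neither p nor q.

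**The case against.** The strongest case against has four parts.

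- **Oversight exists.** The DMEC receives AE reports and holds the unblinded data, and the number and nature of all AEs are recorded. This stands. A reader might infer that such events escape independent and committee review altogether. That is wrong: what is missed is the case-level causality review and the direct SAE report to the TSC.
- **Admission is not the only gate.** Threat to life and lasting incapacity are separate criteria. This also stands, and it limits the point to events that meet no item. It is tempting to say that seriousness depends on local bed thresholds and so differs between the three Trusts. The documents give no admission practice for any of them, and randomisation is stratified by site, so differences between Trusts would not by themselves unbalance the arms.
- **These are not named trial risks.** Suicide appears as a background rate. Harm to others appears only in an exclusion criterion checked at referral or eligibility review, which may also lower the number of events. A reader might infer that the protocol identifies suicide attempts and violence as key risks and then fails to capture them. The text does not go that far, and violence by participants is never listed as a risk of the trial.
- **The article is condensed.** The full protocol and the adverse event form are not shown, and guidance on grading self-harm may sit there. This has less force. The point does not rest on missing detail: the article states a complete definition, and that definition, followed exactly, produces the result in the fourth row.

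**Conclusion.** The point holds in a limited form. The SAE definition is closed and has no medically-important-event criterion. A suicide attempt or serious self-harm that is neither life-threatening nor disabling and does not lead to admission is a non-serious AE. It loses the review by the Chief Investigator and independent rater and the SAE report to the TSC, and is left with individual review by a Site Lead who supervises the therapists. DMEC oversight through AE reports remains.

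The conclusion rests on two readings: that the SAE list is exhaustive, and that an attempt of this kind counts as an AE at all, most naturally as a worsening of illness.

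Its size cannot be derived from the documents. Purely assumed values show this: p from 3% to 8% gives 130 × 0.03 = 3.9 to 130 × 0.08 = 10.4 people, and q from 30% to 70% gives 3.9 × 0.3 = 1.2 to 10.4 × 0.7 = 7.3 events. That range reflects only the values put in and should not be cited as an expected undercount.

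The consequence is for safety classification and reporting. Nothing in the primary outcome, the analysis model or the power is affected.

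**What to change.** Add to the end of the SAE definition in {22}: *or any other event judged medically important, including suicide attempts and serious self-harm, whether or not hospitalised*. Make the same change on the adverse event form. These events then follow the SAE route that already exists, with no new committee or procedure.

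If the investigators also want to capture serious harm to others, amending the SAE list is not enough. The AE definition must be widened first, because an act against another person is not clearly a sign, symptom or illness of the participant.

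If the full protocol already contains such a criterion, the article's definition should be brought into line with it.

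The change affects reporting only, not care. It costs one clause, a slightly higher SAE count and a few more reports for the Chief Investigator, the independent rater and the TSC. If it is made after recruitment has begun, AEs already recorded should be reclassified under the new definition so that one rule covers the whole trial.
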